#### Exercise program rationale

The main aim of the current exercise program is to reduce the loss of bone and lean mass that is commonly observed after BS. Maintaining lean mass is crucial as it helps to preserve the basal metabolic rate, which often declines after BS [29], and may negatively affect body mass loss and body mass maintenance in the long run. Avoiding the loss of lean mass will lead to the preservation of muscle strength, enabling individuals to engage in more intense physical activity and improve their quality of life. Moreover, it is possible that an exercise intervention may also have a positive effect on cardiovascular markers and the gut microbiota.

High-impact exercises that involve jumping and high-speed changes of direction have been demonstrated to be the most effective in improving bone mass [30]. However, these exercises are contraindicated for individuals with obesity, as the additional weight they carry can cause adverse effects on the joints. This is due to the high forces generated during these activities. Therefore, an alternative intervention that has demonstrated efficacy in enhancing bone and lean mass, reducing fat mass, and improving some cardiometabolic markers is training with WBV platforms. A review conducted by Zago et al., which included 18 studies with obese patients, demonstrated that WBV training can improve bone and lean mass [31].

A 16-week training program was selected based on a previous study that included a large number of clinical trials, which found positive effects of exercise interventions that lasted more than 3 months [32]. A 16-week intervention was deemed appropriate, given that bone adaptation requires a longer period than that of lean and fat mass. Although the present protocol includes elastic band training, which could also mask the WBV results, this type of training is only performed for the first 6 weeks. Its purpose is to improve muscle strength in the upper limbs and core, in order to work them out in the next 10 weeks with the WBV platform.

#### Intervention description

##### Supervision and adherence

All training sessions will be overseen by a sports scientist with prior experience in working with WBV platforms. The training will be conducted on a one-to-one basis, with the trainer guiding the participant through each session.

The trainer will contact participants each week via WhatsApp to schedule the upcoming training sessions. The training will be provided free of charge for all participants and will be conducted at the GENUD-Lab (University of Zaragoza, Spain), with no home-based component. The laboratory is equipped with a dedicated space for WBV training and a Smith machine, which will be employed for the attachment of elastic bands and the development of the elastic band training.

During each training session, the trainer will record the following information in each participant’s training book:Date and the participant’s attendance at the training sessionWarm-up: Cycling Watts, perceived exertion (using a validated OMNI scale specific for cycle ergometer [33]) and heart rate (using a Polar H10 heart rate sensor)WBV training: heart rate and perceived exertion (using a validated visual scale [34] specific for WBV) at the midpoint and conclusion of the training sessionElastic band training: the color of the elastic band, heart rate, and perceived exertion (using a validated visual scale specific for Thera-Band bands [35])Adverse effects during the session (pain, discomfort, etc.)Exercises performed by the individual during the previous 72 h outside of the laboratory

At the conclusion of each month, the trainer will evaluate the participant’s attendance percentage and offer constructive feedback to those with a high attendance rate. For those with a low attendance rate, the trainer will discuss potential causes and solutions to improve attendance. In order to progress to the subsequent week, a minimum of two sessions of assistance is required. For instance, should a participant complete only one session in week 5, the following week they will perform one session of week 5 and two sessions of week 6, rather than three sessions of week 6. This adaptation ensures that the increase in intensity is gradual and therefore more manageable. There are no other criteria for discontinuing or modifying allocated interventions. Participants may withdraw voluntary from the trial at any point. They may provide no reason for their withdrawal or may provide any reason they see fit.

All participants will continue with their usual pharmaceutical care during the trial. There is no restriction on accessing external therapy or exercise groups.

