**Discussion:**

Both groups are expected to experience improvements in most of the aforementioned variables. Nonetheless, we expect the WBV group to show larger improvements proving that the training is effective and safe.

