A recent meta-analysis comprising 22 studies evaluating BS patients found that the decrease in BMD was larger in the femoral neck than in the lumbar spine [15]. Additionally, a time-dependent loss of BMD was observed, with larger decreases found in longer follow-up periods. This is consistent with another recent meta-analysis that included 14 studies which evaluated volumetric BMD and bone quality finding negative effects of Roux-en-Y gastric bypass on these variables [16]. The growing evidence of the adverse effects of BS on bone is clear, with the European Calcified Tissue Society publishing a position statement in 2022 stating that BS is associated with a 21–44% higher risk of all fractures [17].

The reduction in BMD may be attributed to a number of factors, including mechanical unloading resulting from a loss of body mass, loss of muscle mass, impaired calcium absorption, changes in hormonal status, and increases in bone marrow adiposity [17]. These factors may also increase the risk of fractures due to alterations in the center of mass, walking biomechanics, and a reduction in muscle mass and strength of the lower limbs. A recent meta-analysis demonstrated that post-surgery exercise interventions can have a positive effect on BMD [18]. In addition, exercise has been shown to have beneficial effects on gut microbiota composition and diversity [19–21] and in reducing inflammation [21, 22]. However, the meta-analysis only included three studies that combined resistance and aerobic training in two to five weekly sessions with an average duration of 45 min per session. Although these interventions are interesting, they require a significant amount of material and space, which makes them difficult to develop. Consequently, shorter and simpler interventions that can be performed in medical clinics and hospitals are needed to maintain participant motivation and avoid the need for a lot of space and equipment.

Whole-body vibration (WBV) training may be a potential solution, as this type of training has demonstrated to be effective in improving body composition and strength in obese patients [23, 24]. Research from our group has shown that it can also improve balance [25] and bone mass [26] in populations with compromised bone mass. In addition, the vibrating platform is only about 1 m^2^, so training can take place in a small space. Therefore, it could be an ideal method for clinics and hospitals to implement.

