## Material and methods

### Study design, research ethics approval, protocol registration, and reporting

This protocol is a two-arm superiority randomized controlled trial. It has been registered in Clinicaltrials.gov NCT05695599 and approved by the Ethics Committee of Clinical Research of Aragón (CEICA, Spain) with reference number C.I. PI22/380. In the event that changes to the protocol are necessary during its implementation, permission will be sought from the Ethics Committee before applying the changes. Participants will be randomly assigned to one of two groups: (1) the control group (CG) or (2) the WBV group. The study design and this protocol manuscript adhere to the SPIRIT reporting guidelines and the SPIRIT 2013 checklist is presented in Supplementary Table 1 [27]. Moreover, the exercise intervention is explained in accordance with the Consensus on Exercise Reporting Template (CERT): Explanation and Elaboration Statement [28]. The 16 items that should be completed in accordance with the CERT are presented in Supplementary Table 2.

As illustrated in Fig. 1, the study will span a period of 18 months. Four different assessments will be conducted at various intervals: T1 (approximately 1 week before the surgery), T2 (7 ± 1 weeks post-surgery), T3 (24 ± 2 weeks post-surgery), and T4 (18 months ± 2 weeks post-surgery).

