##### Training frequency, intensity, and duration

Those allocated to the WBV group will attend three weekly supervised sessions for 16 weeks, with a total of 47 sessions completed (during the first week, only two sessions are performed). Participants will be permitted to select the time of day and day of the week for each session, provided that a minimum of 24 h elapsed between each session and that the training is not performed on three consecutive days.

The duration of the sessions will range from 28 to 46 min, with the intensity increasing weekly through an increase in the number of repetitions, time of vibration, or reduction in rest times as illustrated in Table 1.

In the WBV, all participants will receive the same stimulus, resulting in varying internal loads for each individual. Nevertheless, for the warm-up and the elastic band training, the resistances will be adjusted as previously explained in order to achieve a similar internal load for all participants.

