##### Hospital visits

Anthropometric parameters including body mass (SECA 813), height (Sayol stadiometer), waist circumference, hip circumference, and body mass index will be measured in the hospital. Vital signs including arterial blood pressure (Nellcor N5600) will also be recorded. Any chronic diseases and any acute disease that occurred during the 6 months preceding the onset of the study and any pharmacological treatment or nutritional supplement taken during the previous month will be recorded. Furthermore, all participants will undergo a blood extraction to evaluate the following parameters: hemogram and biochemistry, coagulation indicators, iron metabolism, liver enzymes, bone metabolic markers, C-reactive protein, and interleukin 6, in accordance with standard hospital procedures. In addition, tumor necrosis factor-alpha (TNF-α) levels will be quantified by enzyme-linked assay (ELISA) methodology (Quantikine High Sensitivity Human by R&D Systems, Minneapolis, MN, USA).

#### Day 2

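### The only adverse-effect record described is a log kept in WBV sessions, which cannot support the expected conclusion that the training is safe

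*Protocol article*

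**What the plan says.** Under Supervision and adherence, the protocol article states: "During each training session, the trainer will record the following information in each participant’s training book". One item in that list is "Adverse effects during the session (pain, discomfort, etc". Training frequency, intensity, and duration shows who is covered: "Those allocated to the WBV group will attend three weekly supervised sessions for 16 weeks, with a total of 47 sessions completed". Controls receive standard care and have no sessions.

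The section on Hospital visits adds a history item: "Any chronic diseases and any acute disease that occurred during the 6 months preceding the onset of the study". It also asks about medicines and supplements in the month before.

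Follow-up ends at "T4 (18 months ± 2 weeks post-surgery". The discussion paragraph of the abstract gives the expected conclusion: "we expect the WBV group to show larger improvements proving that the training is effective and safe".

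**The concern.** A statement that an intervention is safe needs events to be sought in the same way in both arms, over the period in which harm could appear. Here the one described record of adverse effects belongs to a single arm and to the minutes spent in the laboratory. No item is described that would capture a fall, fracture or injury as an event in a control participant, in a trained participant between sessions, or in anyone after week 16.

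Any adverse-effect count from this trial would therefore describe how well sessions were tolerated. It could not show whether trained participants had more or fewer events than controls. This matters beyond the abstract. The main Discussion says that, if the cost-effectiveness results are favourable, the researchers would try to bring the programme into usual care in the national health system, and a reader of that proposal would rely on the safety statement.

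**Working it through.** The article gives no safety figure to reproduce, so the check sets the recording rules beside the conclusion.

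**1. Recording occasions by arm.** Two sessions in week 1 and three in each of weeks 2 to 16 give 2 + 15 × 3 = 47, which matches the stated total. As described, adverse effects are noted on up to 47 occasions per WBV participant and on 0 occasions per control participant.

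**2. Calendar cover.** T2 is at 7 weeks, T3 at 24 weeks and T4 at 18 months, or about 78 weeks. The 16-week programme fits between T2 and T3. It spans 16/78, about 20% of follow-up, in one arm only. From T3 to T4 there are 78 − 24 = 54 weeks with no described adverse-effect record in either arm.

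**3. Are the windows chosen or merely abbreviated?** Two contrasts suggest that they are stated rules. The training-book list looks back 72 h outside the laboratory for exercise, but confines adverse effects to the session. The hospital item looks back one month for medicines, but ties acute illness to the start of the study. Repeated word for word at T2 to T4, the acute-illness clause would collect no new acute event.

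**4. What else is collected in both arms.**

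| Source (section) | Reach | Identifies and classifies an event? |
|---|---|---|
| WOMAC knee and hip pain | to T4 | No, a pain score |
| EQ-5D-5L and SF-36 | to T4 | No, a health-state score |
| DXA and pQCT | to T4 | No, a bone measurement |
| Blood markers (Hospital visits) | to T4 | No, laboratory values |
| Chronic disease, recent medicines (Hospital visits) | no clear window; previous month | Indirectly at most |
| Healthcare use, including emergency care, hospital days, imaging, physiotherapy, medication (Cost-effectiveness analysis) | about 6 months | Leaves a trace if care was sought, recorded as a cost |

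The Outcome variables section puts the outcome measures at four time points. Where a measure skips a visit (diet, stool) the article says so, and no such exception is stated for the first three rows or the blood markers.

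**5. The word proving.** If no event of a given kind occurred among n trained participants, the exact one-sided 95% upper limit for its risk is 1 − 0.05^(1/n). This gives 19.3% for n = 14 and 22.1% for n = 12. These limits reflect the sample size only. They do not measure the recording gap and would be the same under better recording, but they show why proof of safety is out of reach at this size.

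**The case against.** The strongest reply is that this is a condensed article. A full protocol, or the SPIRIT and CERT supplements, may contain an adverse-event procedure, so silence here is weak evidence. That stands as a caution: the point is confined to what the article states, namely a one-arm, in-session rule beside a safety conclusion.

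Four stronger readings are tempting, and the documents do not support them.

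- A reader might infer that there is no control-arm comparison and no follow-up to 18 months for anything relevant to safety. Pain, quality-of-life and bone measures run to T4 in both arms, and healthcare use covers about 6 months.
- A reader might infer that later illness is deliberately excluded. The sentence under Hospital visits reads as baseline history, and its chronic-disease and medication items could reflect in-study events if repeated. But if it is baseline history only, the article describes no in-study illness record.
- A reader might infer that the trial will tabulate WBV events against none in controls. No such comparison is planned, and safety is not among the objectives, the primary outcomes or the stated analyses. The claim rests on one sentence of the abstract.
- A reader might take "BS is associated with a 21–44% higher risk of all fractures" as a harm that separates the arms. It concerns surgery, which both arms undergo. It shows that fractures matter in this population, but says nothing about WBV against control.

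**Conclusion.** The mismatch is real and should be corrected. As described, adverse effects are recorded in one arm, in sessions, within about 20% of follow-up, and no item identifies and classifies falls, fractures or injuries by arm up to T4. The measures shared by both arms soften the gap without closing it. The data collection supports a statement on in-session tolerability, not a conclusion that the training has been proven safe.

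This rests on reading the session log as confined to the WBV arm, which follows from controls having no sessions, and on no fuller adverse-event procedure existing elsewhere. If one does exist, the article's text should be aligned with it. If the cost-analysis window runs from surgery (its start is not given), healthcare-use records would span the training period but would still stop about a year before T4. The efficacy analyses are unaffected.

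**What to change.** 1. At the existing T2, T3 and T4 visits, ask both arms the same fixed adverse-event question, covering falls, fractures, injuries and new illness since the previous assessment. Use existing staff, with a blinded assessor where feasible. The nurse is named as blinded, but the article does not say who takes the hospital history, so this has to be assigned.
2. Report these events by arm to T4, descriptively, with exact confidence intervals.
3. Report the session log separately, as tolerability of WBV training.
4. Replace the abstract's wording on proof of safety with a statement about tolerability and observed event rates.

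The cost is one form change and a few minutes per visit. Recall will be imperfect over the T3 to T4 gap of about 54 weeks, answers may unblind the person asking, and the safety claim becomes weaker. If data collection can no longer change, step 4 alone removes the contradiction at no cost.

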#### Eligibility criteria

Inclusion criteriaIndividuals undergoing a SG with a BMI above 40 kg/m^2^ and a body mass of less than 180 kgAged between 18 and 50 years

Exclusion criteriaHave suffered any type of cancer in the last 5 yearsHave a pacemaker or have been diagnosed with a cardiac problem that disables the patient from participating in an exercise programHave suffered an acute myocardial infarction in the last 6 monthsHave recently suffered a fractureHave any other condition that the physician deems as a contraindication for performing supervised physical exercise

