##### Session structure

The structure of the sessions will be:AWarm-up

The warm-up will entail cycling at a frequency between 60 and 70 revolutions per minute. This will be performed on an electromagnetic cycle ergometer (Ergoline Viasprint150p). The initial session will be conducted with a 60-W resistance load. Subsequently, individual adjustments in the watt resistance will be made in order to achieve a moderate activity level (a score of 4–5 on a 0 to 10 scale) on a validated OMNI scale specific to cycle ergometer [33]. Consequently, in the event that a participant indicates a score of less than 4 on the OMNI scale, the resistance will be increased by 5 W in the next session.

BWBV training

The WBV will be performed on a synchronous vertical vibration platform (Power Plate® Pro5; PowerPlate, Amsterdam, The Netherlands) with the participant positioned barefoot and with a contoured mat provided by Power Plate®. The WBV protocol is presented in Table 1. The protocol details for months 1–4 can be found in Supplementary Tables 3, 4, 5, and 6, respectively. Prior to commencing the WBV session, the supervisor will provide an explanation of the exercises to be performed during the session. All exercises will be performed with both the forefoot and the heel touching the platform, with the exception of calf raises and bent knee calf raises, which will be performed without contact of the heel with the platform. In order to prevent skidding on the mat provided by the Power Plate, participants will wear socks. As specified in Fig. 2, all exercises will be performed with flexion of at least one lower limb joint in order to prevent vibrations from being transmitted to the head. At the beginning of each month, novel exercises will be introduced, and participants will be allowed to grasp the WBV platform handrail with both hands in order to perform the exercises during the first week. In the subsequent week, participants will be instructed to perform the exercise with one hand only. Over the course of the final weeks of each month, they will be encouraged to progress to a position where they are able to perform the exercises without holding on to the handrail, as detailed in Supplementary Tables 3, 4, 5, and 6. It is important to note that no dumbbells or resistance bands will be utilized during the performance of exercises on the Power Plate®.

**Table 1 Tab1:** WBV protocol

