**Fig. 2 Fig2:**
[figure not shown]
Elastic band and WBV exercises. Exercise X is an exercise that starts with the participant standing on a step and advancing one leg to step on the WBV platform finishing in split squat position (exercise V) to then go back to standing up on the step and repeating with the other leg. Exercise XI is a dynamic squat from 120 to 90°

As illustrated in Table 1, complementary exercises will be conducted during the initial 6-week period and are elucidated in detail in Fig. 2 and in the “Elastic band training” subsection described below. During certain weeks, the complementary exercises will be performed on the WBV platform without the device being activated as a means of familiarization, while in the following weeks, the same exercises will be performed with the vibration stimulus.C.Elastic band training

The initial 6-week phase of the WBV training program will be accompanied by an elastic band training component. All exercises will be performed at a speed of 2 s for the concentric phase and 2 s for the eccentric phase. The exercises will be performed using Thera-bands (Thera-Band, Hadamar, Germany). Participants will start with the yellow band and perform the exercises until they reach approximately a 200% elongation at the conclusion of the concentric phase. As participants progress, they will increase the intensity of the exercises using different colors of bands. The tension generated by each band at a 200% elongation is as follows: yellow (1.69 kg-force (kgF)), red (2.26 kgF), green (2.91 kgF), blue (3.52 kgF), black (5.23 kgF), silver (5.91 kgF), and gold (7.55 kgF) [36]. At the conclusion of the final circuit of the day, a visual scale designed for Thera-Band bands [35] will be employed. Should participants indicate a perception below 5 (“somewhat hard”) on a scale of 10, a harder band will be used in the next session.

During the first week, the exercises will be performed after the WBV training. Participants will perform a circuit of four exercises (chest fly, biceps curl, row, and triceps kickback (Fig. 2)) with 12 repetitions per exercise and a 1-min rest interval between each exercise. The circuit will be repeated twice during the second week. The first repetition will be performed after the fifth WBV repetition and the second after the tenth WBV repetition: 5 WBV repetitions, circuit (4 exercises * 12 reps), 5 WBV repetitions, circuit (4 exercises * 12 reps), 5 WBV repetitions.

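### The protocol states that no criterion other than attendance modifies or stops the vibration programme, so no medical event has a stated consequence for the vibration dose

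*Protocol article*

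**What the plan says.** The Supervision and adherence section gives one rule that alters the prescribed programme: "In order to progress to the subsequent week, a minimum of two sessions of assistance is required". It illustrates this with a participant who attends once in week 5 and then makes up one week 5 session before doing two from week 6. It continues: "There are no other criteria for discontinuing or modifying allocated interventions". The next sentences allow participants to leave the trial voluntarily at any time, with or without a reason.

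The same section has the trainer, a sports scientist, record attendance, heart rate, perceived exertion and adverse effects in a training book. No action is attached to the adverse-effect entry, or to the heart rate and exertion taken during vibration.

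Training frequency, intensity, and duration fixes the dose: "In the WBV, all participants will receive the same stimulus, resulting in varying internal loads for each individual". Load is individualised only elsewhere. In the warm-up, "individual adjustments in the watt resistance will be made in order to achieve a moderate activity level". In the elastic band training, when exertion is rated low, "a harder band will be used in the next session".

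Eligibility criteria excludes people with a recent fracture, an infarction in the last 6 months, a pacemaker or disabling cardiac problem, or "any other condition that the physician deems as a contraindication for performing supervised physical exercise". These are conditions of entry. The document does not apply them again during training.

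**The concern.** A condition serious enough to bar someone from supervised exercise at entry has no stated consequence if it appears during the 16 weeks. This is a positive statement that no further criteria exist, so it cannot be read as detail left to a fuller protocol or an analysis plan. A fuller document that contained medical criteria would contradict it.

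Two things are at stake. The first is participant safety: the trainer has no written criterion on which to reduce or stop the vibration, or to ask a physician to decide, while the prescribed dose rises overall. The second is the data. The only documented way out is to withdraw from the trial, so a participant who should merely stop training may be lost to follow-up. The abstract also expects the trial to show that the training is safe, which is harder to argue when the response to a safety event is undefined.

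**Working it through.** **1. Search for a medical rule.** Each place that could supply one was read against the sentence in question.

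| Place | What it provides | Pauses, reduces or stops vibration on medical grounds? |
|---|---|---|
| Eligibility criteria | Medical exclusions | No, entry only |
| Supervision and adherence, progression rule | Slows progression after missed sessions | No, attendance only |
| Supervision and adherence, training book | Records adverse effects, heart rate, exertion | No action attached |
| Supervision and adherence, withdrawal | Participant may leave the trial | No, the participant's choice |
| Session structure (warm-up) | Wattage set by exertion; the explicit step is +5 W | No, not vibration |
| Elastic band training | Harder band if exertion is below 5 | No, not vibration |
| Training frequency, intensity, and duration | Same vibration stimulus for all | No, fixes the dose |

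**2. Prescribed vibration time.** Formula: repetitions × seconds, summed over the vibration exercises in Table 1.

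This reading of the table reproduces its own session length. In week 16 every repetition plus its rest takes 60 s and there are 11 + 4 + 7 + 5 + 6 = 33 repetitions. That gives 33 min, plus 10 min warm-up and 2 min rest = 45 min, as stated.

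- Week 1: 10×20 = 200 s
- Week 8: 12×30 + 12×30 + 5×15 = 795 s
- Week 10: 11×30 + 11×30 + 4×30 + 6×30 = 960 s
- Week 11: 10×30 + 2×15 + 10×30 + 3×30 + 5×30 = 870 s
- Week 12: 7×45 + 3×15 + 7×45 + 4×30 + 5×30 = 945 s
- Week 13: 9×45 + 4×15 + 5×30 + 4×15 + 5×30 = 825 s
- Week 16: 11×45 + 4×20 + 7×45 + 5×20 + 6×45 = 1,260 s

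The ratio of week 16 to week 1 is 1,260/200 = 6.3. Time falls between weeks 10 and 11 and between weeks 12 and 13. In week 13 squat displacement goes from 1 to 2 mm while squat frequency goes from 35 to 30 Hz. The dose therefore rises overall but not monotonically.

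**3. Exposure and the per-protocol threshold.** Sessions: 2 + 15×3 = 47, matching the stated total. Threshold: 0.70×47 = 32.9, so 33 sessions (33/47 = 70.2%; 32/47 = 68.1%), or at most 14 missed. With perfect attendance, 2 + 3×10 = 32 sessions are done by the end of week 11 and 35 by the end of week 12. Even a fully adherent participant stopped by the end of week 11 leaves the per-protocol set.

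**4. What happens to a stopped participant in the analysis.** Neither intention-to-treat definition requires attendance at training, but they differ. Statistical methods needs baseline plus at least one assessment after assignment. Cost-effectiveness analysis needs completion of the trial. Someone who stops training and also leaves follow-up is lost from the second set, and from the first unless a later assessment was already made. Retention therefore depends on continued follow-up, which the protocol does not state for participants stopped on medical grounds.

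**The case against.** The strongest reply is that the sentence closes a paragraph about adherence and says only that no further criteria are pre-specified. A reader might infer that training must continue after a fracture or infarction. The text does not say that and does not forbid clinical judgement. This limits the point to the absence of a stated rule.

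Safeguards exist. Each session is supervised one to one, standard care continues in both arms, a sports and exercise physician conducts the exercise test, and the ethics committee has approved the study. Someone too ill to attend also progresses more slowly. All of this makes harm less likely, but none of it is a criterion for changing the vibration. The attendance rule delays the schedule without lowering the dose of the next session attended.

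Three further inferences are not supported:

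- Attendance is not the only stated brake, because voluntary withdrawal is available at any point. It is the participant's choice, however, and it ends trial participation rather than only training.
- The 6.3-fold rise is not a smooth climb, and it starts from a deliberately light first week. It describes dose and does not measure harm.
- The background statement that "BS is associated with a 21–44% higher risk of all fractures" is a relative figure for bariatric surgery in general. It says nothing about how many fractures to expect in 16 weeks after sleeve gastrectomy.

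**Conclusion.** The point holds and should be fixed. Beyond attendance, the protocol states that no criterion modifies or discontinues the intervention, and no other section supplies a medical one for the vibration dose. It applies to the 14 planned participants in the vibration arm, over 47 sessions each, with prescribed vibration rising overall from 200 s to 1,260 s per session.

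The number of participants likely to be affected cannot be stated, because the document gives no event rate and none is assumed here. Error rate and power are not in question. The conclusion rests on reading the sentence as written and on Table 1 listing seconds per repetition, which its session lengths support. It does not rest on any claim that the trainer would act unsafely. Nor can a reader assume that medically stopped participants are already secure in the intention-to-treat sets. That holds only if they stay in follow-up.

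**What to change.** Replace the sentence with a rule along these lines: training is paused, reduced or stopped if a fracture, an infarction, a disabling cardiac problem or another physician-judged contraindication arises, or whenever a physician judges training contraindicated; a significant adverse effect in the training book triggers that review. The clinical thresholds are for the sponsor and the treating physicians.

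Add that stopping training is not withdrawal from the trial. Such participants attend T3 and T4 and are analysed in their allocated arm. They need this to remain in the economic set of trial completers and in the statistical set of those with baseline and a later assessment.

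The cost is a short amendment, submitted to the ethics committee as the protocol requires, using data already recorded and adding no visits or measurements. The downside is small: some participants receive less than the full programme, and anyone with fewer than 33 of 47 sessions leaves the per-protocol set.
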